## Abstract

**Background:**

Impingement can be a serious complication after total hip arthroplasty (THA), and is one of the major causes of postoperative pain, dislocation, aseptic loosening, and implant breakage. Minimally invasive THA and computer-navigated surgery were introduced several years ago. We have developed a novel, computer-assisted operation method for THA following the concept of "femur first"/"combined anteversion", which incorporates various aspects of performing a functional optimization of the cup position, and comprehensively addresses range of motion (ROM) as well as cup containment and alignment parameters. Hence, the purpose of this study is to assess whether the artificial joint's ROM can be improved by this computer-assisted operation method. Second, the clinical and radiological outcome will be evaluated.

**Methods/Design:**

A registered patient- and observer-blinded randomized controlled trial will be conducted. Patients between the ages of 50 and 75 admitted for primary unilateral THA will be included. Patients will be randomly allocated to either receive minimally invasive computer-navigated "femur first" THA or the conventional minimally invasive THA procedure. Self-reported functional status and health-related quality of life (questionnaires) will be assessed both preoperatively and postoperatively. Perioperative complications will be registered. Radiographic evaluation will take place up to 6 weeks postoperatively with a computed tomography (CT) scan. Component position will be evaluated by an independent external institute on a 3D reconstruction of the femur/pelvis using image-processing software. Postoperative ROM will be calculated by an algorithm which automatically determines bony and prosthetic impingements.

**Discussion:**

In the past, computer navigation has improved the accuracy of component positioning. So far, there are only few objective data quantifying the risks and benefits of computer navigated THA. Therefore, this study has been designed to compare minimally invasive computer-navigated "femur first" THA with a conventional technique for minimally invasive THA. The results of this trial will be presented as soon as they become available.

**Trial registration number:**

DRKS00000739

## Background

One of the great intraoperative challenges in total hip arthroplasty (THA) is to find an optimized compromise between hip biomechanics, tribology and post-operative functionality. Component malpositioning and soft tissue imbalance influence the prevalence of dislocation, loosening, wear, containment, postoperative range of motion (ROM) and impingement. Impingement can be caused through component-to-component contact (periprosthetic impingement), bone-to-bone contact (bony impingement) or component-to-bone contact (bone-to-prosthesis impingement). Bone-to-bone impingement is usually correlated to the offset of the prosthesis while component-to-component impingement is highly dependent on the design and position of the total joint components. The surgeon's intraoperative task is to weigh stable cup containment against optimal postoperative ROM with no impingement [1-6]. Traditionally, THA begins with the preparation of the acetabulum and implantation of the prosthetic cup, followed by the preparation of the femoral cavity and stem insertion. In cementless THA performed manually, the antetorsion of the femoral stem is usually hard to control. Depending on the anatomical shape of the femur, the broaches and the definitive implant virtually "find their way" to a rotational position, where the stem conforms best to the rigid shape of the native proximal femur canal. This results in a wide variability of stem antetorsion from 15° of retroversion to 45° of anteversion on the postoperative CT scans [1,7,8]. In contrast, cup inclination and cup anteversion can be controlled to a certain extent by the surgeon during the reaming and implantation process. Multifold models have been developed to determine the optimal combination of cup inclination, cup anteversion, and stem antetorsion for maximizing ROM and minimizing the risk for impingement. In this context, different authors have proposed starting with the preparation of the femur ("femur first") and then adjusting the position of the cup in accordance to the femoral rotation. For a secure component fixation and orientation, the sum of the stem antetorsion and cup anteversion, known as "combined (ante)version", must then fall within one of the following criteria: close to 45° for women/between 20°-30° for men, according to Ranawat; between 40°-60°, according to Jolles; between 25°-50°, according to Dorr; or it should satisfy the equation give by Widmer, i.e. cup anteversion + (0.7 × stem antetorsion) = 37.3° [2,9-11]. This complementary component orientation should ensure proper alignment of the femoral head within the cup without impingement of the two throughout all body positions, and has been referred as the "zone of compliance" [11].

In the past, computer navigation has improved the accuracy of component positioning. Non-image based or imageless navigation systems, which do not require additional pre- or intra-operative image acquisition, have demonstrated their ability to significantly reduce the variability in positioning the acetabular component and have shown to precisely measure leg length and offset changes during THA [12-15]. Nowadays, these navigation systems also have the prowess to couple three dimensional simulations with real time evaluations of surgical performance [16].

Hence, the purpose of this study is to conduct a patient- and observer-blinded, randomized controlled trial with a newly developed computer-assisted operation method for THA following the concept of "femur first"/"combined anteversion," which includes various aspects of a functional optimization of the cup position and comprehensively addresses ROM as well as containment and alignment parameters. It is our hypothesis that minimally invasive computer-navigated "femur first" THA will lead to an increased ROM without bony or periprosthetic impingement. The present paper reports on the methodological design of the study.

## Methods/Design

### Study design

A patient- and observer-blinded randomized controlled trial will be conducted. Patients will be randomly allocated to receive minimally invasive computer-navigated "femur first" THA or the conventional minimally invasive THA procedure. The random allocation sequence will be computer-generated in a permuted block randomization design by one of the associate statisticians (TS, KU) using certificated randomization software (Rancode 3.6 Professional, IDV, Gauting, Germany). Permuted blocks of size 4, 6 and 8 participants will be employed to ensure a balanced allocation sequence. This sequence will then be placed into sealed, consecutively numbered, opaque envelopes. These envelopes will be kept in a locked filing cabinet in the office of the surgeon who will open the envelopes in order of participant recruitment. The random allocation sequence will not be revealed to the clinical examiners conducting the baseline or follow-up assessments and will only be opened by the study surgeon upon notification of completion of the baseline assessment by the clinical examiner.

The study design, procedures and informed consent are approved by the Medical Ethics Committee of Regensburg University Medical Center (No.: 10-121-0263). The trial is registered at the German Clinical Trials Register and the registry platform for international clinical trials of the World Health Organization (WHO) under the same Main ID DRKS00000739.

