### Study population

The study will be conducted at the Orthopedic Department of Regensburg University Center, Asklepios Klinikum Bad Abbach, Germany. Patients between the ages of 50 and 75 with an American Society of Anesthesiologists (ASA) score ≤ 3 who are admitted for primary cementless unilateral THA due to primary or secondary osteoarthrosis will be included. Participation in the study is voluntary and patients have to provide informed consent (incl. consent to the postoperative computed-tomography scan) before participation. Exclusion criteria include an ASA score > 4, pregnancy, THA on the contralateral side and inability to understand the consent form. The inclusion period is planned from June 2011 to August 2012.

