### Intervention

Both groups will have surgery using the minimally invasive single-incision Micro-Hip^® ^approach in a lateral-decubitus position [17]. In brief, the surgical approach begins with an incision midway along the greater trochanter on its ventral edge and runs for 6-8 cm in the direction of the anterior superior iliac spine. Then, the subcutis is severed, revealing the iliotibial tract and the fascia. After incision of the fascia, the approach follows the interval between the tensor fascia lata muscle and the rectus muscle using a section of the anterior iliofemoral approach described by Smith-Petersen. No tendon or muscle is cut or detached. The joint capsule is split and left in place. The hip joint is not dislocated, the osteotomy of the femoral neck is performed in situ. The head is then removed. An angulated, minimally invasive instrument with a double offset will be used in all operations in order to facilitate muscle sparing reaming and insertion of the cup and stem. The leg is extended, adducted and externally rotated in order to prepare the femur. After final reposition the fascia and skin are closed [17]. Press-fit acetabular components and cement-free hydroxyapatite-coated stems (Pinnacle cup, Corail stem, DePuy, Warsaw, IN, USA) with metal heads will be used in both groups. The intra- and postoperative definition of the acetabular planes for cup inclination and anteversion will rely on the same Murray (radiographic) plane and coordinate system in both groups [18].

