#### Primary endpoint definition and sample size justification

Sample size calculation is based on the primary hypothesis that minimally-invasive computer-navigated FF THA group will lead to an increased ROM with no impingement. Accordingly, the primary endpoint to be comparatively assessed in this study will be the proportion of patients showing post-surgery optimal ROM configurations without osseous or metallic impingement. The Chi-square test will be used for statistical assessment of the primary study hypothesis. In order to detect differences of at least 25 percentage points in the primary outcome criteria between the study groups at a two-sided significance level of 5% with 80% power, a group sample size of 60 patients is required. Considering an expected dropout rate of 5%, a total of 128 patients will be included in the study. Additionally, a learning sample of 5 patients will be incorporated to allow the surgeons to familiarize themselves with the novel prototype software.

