#### Statistical analysis

The statistical analysis will be performed using the statistical software SAS (SAS Institute Inc., Cary, NC, USA) and R (R Foundation for Statistical Computing, Vienna, Austria). The primary efficacy endpoint will be assessed based on the intention-to-treat (ITT) population. Therefore, all patients will be considered as randomized in the analysis. A two-sided Chi-square test at a 0.05 level of significance will be used for the statistical confirmatory analysis. Ninety-five percent confidence intervals will be provided for the difference in proportions and the estimated risk ratio. For the purpose of sensitivity analysis, per protocol- and complete case analysis of the primary endpoint will be conducted and additional missing-value replacement strategies will be employed. Analysis of secondary endpoints will be conducted as appropriate.

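### The envelope is opened once baseline is complete, with no requirement that this happen at the operation, so patients lost before surgery are randomised without a possible endpoint (minor)

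*Protocol article*

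**What the plan says.** All references are to the protocol article.

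- **Study design.** The sequence "will only be opened by the study surgeon upon notification of completion of the baseline assessment by the clinical examiner". The envelopes lie in a locked cabinet in the office of the surgeon, "who will open the envelopes in order of participant recruitment". No day, place or interval relative to surgery is given.
- **Study population.** Patients "who are admitted for primary cementless unilateral THA due to primary or secondary osteoarthrosis will be included".
- **Intervention.** "Both groups will have surgery using the minimally invasive single-incision Micro-Hip" approach, with the same patient position and the same cup and stem models. The conventional group gets the same stab incisions as the navigated group, to keep patients blinded. The navigation is imageless, and its landmarks are registered during the operation.
- **Primary endpoint definition and sample size justification.** The endpoint is "the proportion of patients showing post-surgery optimal ROM configurations without osseous or metallic impingement". Under Radiographic evaluation it is computed from the postoperative CT. On numbers: "Considering an expected dropout rate of 5%, a total of 128 patients will be included in the study".
- **Statistical analysis.** "The primary efficacy endpoint will be assessed based on the intention-to-treat (ITT) population", and "Therefore, all patients will be considered as randomized in the analysis". Per-protocol analysis, complete-case analysis and missing-value replacement are listed as sensitivity analyses.

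**The concern.** The only trigger named for opening the envelope is that baseline is finished. Some time passes between that point and the first incision, and a patient may withdraw or be cancelled in it. Once the envelope is open, such a patient is randomised and belongs in the primary analysis, yet no CT of an implanted hip can exist. The outcome must then be imputed or the patient left out.

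Two things are at stake. The first is a few avoidable missing endpoints. The second is that these losses may not be independent of arm. Patients and observers are blinded, but the surgeon opens the envelope and cannot be. In this interval the surgeon knows the allocation and can still influence whether the operation takes place. Opening the envelope at the operation removes both problems, and the described procedures give no reason to open it sooner.

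**Working it through.** **1. The plan's own figure.** Inputs: 60 evaluable patients per group and 5% dropout (Primary endpoint definition and sample size justification).

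- 60 / (1 − 0.05) = 63.2, rounded up to 64 per arm, so 2 × 64 = 128. This matches the stated total.
- The margin is 128 − 120 = 8 patients, or 8/128 = 6.25%.
- The base rates behind the 60 are not stated. The uncorrected chi-square formula (two-sided 5%, 80% power) gives 58 per arm for 25% v 50%, 61 for 30% v 55%, 62 for 37.5% v 62.5% and 58 for 50% v 75%. The 60 is therefore reproduced within 2 patients for mid-range rates.

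**2. When the arm has to be known.** Approach, position and implants are common to both arms, and so are the stab incisions. The arms first differ when the navigation pins go in through those incisions. No arm-specific step before surgery is described for the patient. Earlier opening helps only with planning equipment.

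**3. Which patients lose the endpoint.**

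| Event after the envelope is opened | In the ITT set? | CT-based endpoint possible? |
|---|---|---|
| Withdraws before surgery | Yes | No |
| Operation cancelled | Yes | No |
| Operated on with a different implant | Yes | Yes (protocol deviation) |

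**4. Size.** The share of dropout that falls before surgery is not given. 5% of 64 is 3.2, about 3 patients per arm. *Assumption:* one third to two thirds of these, so m = 1 to 2 per arm, are lost between opening and surgery.

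- Changing one arm's m missing values from failure to success moves the difference by m/64: 1/64 = 1.6 points, 2/64 = 3.1 points.
- The two extreme assignments (all missing favour one arm, or all favour the other) differ by 2m/64: 2/64 = 3.1 points, 4/64 = 6.3 points.

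**5. Scale for comparison.** The design targets 25 points. With 64 per arm and rates near 50%, the uncorrected chi-square boundary is 1.96 × √(2 × 0.25 / 64) = 17.3 points, which in whole patients is 12/64 = 18.75 points. A range of 3 to 6 points could change the result only if it lay close to that boundary.

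**6. Power.** The assumed 2 to 4 pre-surgery losses in total fit within the margin of 8. At assumed rates of 37.5% v 62.5%, complete-case power is 79.5% at 5% loss from 128 randomised, so the allowance does what it was meant to do.

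**The case against.** The strongest reply is that the trigger sentence protects concealment: it stops the envelope being opened before baseline is done. It does not say that opening comes well before surgery. The patients are admitted for the operation, so baseline on admission with surgery soon after fits the text. Randomising after consent and baseline is accepted practice, and keeping every randomised patient is correct ITT. Losses are foreseen through the 5% allowance and the missing-data analyses, and the rule for unoperated patients may stand in an analysis plan that is not shown. No passage suggests that a surgeon would cancel by arm.

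Most of this stands, and it rules out several stronger readings that a reader might infer:

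- *Allocation is known long before surgery.* The interval is not given, and opening just before the operation is not excluded.
- *Patients converted to another implant have no endpoint.* They are still operated on and can have the CT. They are a matter for the per-protocol analysis.
- *The whole 5% dropout is due to timing.* About 3 per arm would give 3/64 = 4.7 points for one arm and 6/64 = 9.4 points between the extremes. However, a missed or refused CT after surgery would remain whenever the envelope is opened, so only an unknown part is avoidable.
- *The sample size is too small on this account.* The allowance covers the loss of power.

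What the reply does not remove is that the stated rule permits opening before the operation, without need, by the one person who is not blinded. A dropout allowance protects power. It does not protect against loss that depends on arm.

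**Conclusion.** The point holds as a minor, inexpensive improvement to a stated rule. The protocol article fixes the trigger at completion of baseline and does not require opening at the operation. Patients lost between the two are in the ITT set and cannot have the endpoint, and the surgeon knows their arm.

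Under the assumption of 1 to 2 such patients per arm, the extreme imputations differ by about 3 to 6 percentage points. This is a bound and not an expected bias, and the assumed count has no source in the document. If baseline and surgery fall close together, the true number may be nearer zero. Loss that differs by arm is possible under the rule, but nothing in the document shows that it is likely. No stated number needs to change.

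**What to change.** Change the sentence under Study design so that, once baseline is complete, the next numbered envelope is opened in theatre on the day of surgery, after eligibility is finally confirmed and immediately before the stab incisions. Envelopes would then be used in order of operation, so the present wording on recruitment order must change with it. Patients who do not reach that point are logged as not randomised, and the envelope goes to the next patient.

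Cost: a small text change, the navigation set ready for every study case, a few minutes of theatre time, and the envelopes brought from the surgeon's office. The sample size and the primary test stay as they are. Implant changes decided after opening, and CT scans missed after surgery, are not prevented and still need the planned ITT, per-protocol and missing-data analyses.

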### Study population

The study will be conducted at the Orthopedic Department of Regensburg University Center, Asklepios Klinikum Bad Abbach, Germany. Patients between the ages of 50 and 75 with an American Society of Anesthesiologists (ASA) score ≤ 3 who are admitted for primary cementless unilateral THA due to primary or secondary osteoarthrosis will be included. Participation in the study is voluntary and patients have to provide informed consent (incl. consent to the postoperative computed-tomography scan) before participation. Exclusion criteria include an ASA score > 4, pregnancy, THA on the contralateral side and inability to understand the consent form. The inclusion period is planned from June 2011 to August 2012.

### Intervention

Both groups will have surgery using the minimally invasive single-incision Micro-Hip^® ^approach in a lateral-decubitus position [17]. In brief, the surgical approach begins with an incision midway along the greater trochanter on its ventral edge and runs for 6-8 cm in the direction of the anterior superior iliac spine. Then, the subcutis is severed, revealing the iliotibial tract and the fascia. After incision of the fascia, the approach follows the interval between the tensor fascia lata muscle and the rectus muscle using a section of the anterior iliofemoral approach described by Smith-Petersen. No tendon or muscle is cut or detached. The joint capsule is split and left in place. The hip joint is not dislocated, the osteotomy of the femoral neck is performed in situ. The head is then removed. An angulated, minimally invasive instrument with a double offset will be used in all operations in order to facilitate muscle sparing reaming and insertion of the cup and stem. The leg is extended, adducted and externally rotated in order to prepare the femur. After final reposition the fascia and skin are closed [17]. Press-fit acetabular components and cement-free hydroxyapatite-coated stems (Pinnacle cup, Corail stem, DePuy, Warsaw, IN, USA) with metal heads will be used in both groups. The intra- and postoperative definition of the acetabular planes for cup inclination and anteversion will rely on the same Murray (radiographic) plane and coordinate system in both groups [18].

#### Minimally invasive, computer-navigated femur first (FF) THA

In the minimally invasive computer-navigated "femur first" (FF) THA group, an imageless navigation system (BrainLAB Navigation System Prototype Hip 6.0 "Femur First", Feldkirchen, Germany) with a newly developed "femur first" prototype software will be used. For the navigation process, reference pins (two Kirschner wires, 3.2 mm diameter) will be inserted into the anterior iliac crest and into the ventro-lateral third of the distal femur after stab incisions are made. Dynamic reference bases will be then attached to the pins. As a next step, the anterior superior iliac spine (ASIS) and pubic tubercle points will be registered using a reference pointer positioned on the skin surface. These points define the reference coordinate system of the pelvis, i.e. anterior pelvic plane and midsagittal plane as the symmetry plane of both ASIS points. On the femoral side, the medial and lateral aspect of the epicondyles and ankle points will be registered. The knee has to be flexed by 90° during the acquisition of the ankle points. These points define the center of the condyles as well as ankle. After osteotomy of the femoral neck and removal of the head, the femur will be exposed. Points at the femoral resection plane will be registered for assessment of bony range of motion. Reaming of the femoral medullary canal will incorporate various measurements of the femoral anatomy using the navigation system, including the entry point of the proximal shaft and the antetorsion. Then, the acetabular anatomy will be registered and reamed. Depending on the information gathered during the femoral and acetabular preparation, the navigation system now calculates an optimized, impingement-free cup position which is presented to the surgeon on a screen. After the insertion of the uncemented acetabular cup in this prescribed position, the uncemented femoral component is placed, followed by placement of a head on the femoral component, repositioning of the joint and closure in layers. All landmark and verification information will be logged by the navigation system for further analysis steps.

